### Secondary outcome measures

The following endpoints will also be considered: 1) the occurrence of histologically proven acute rejection episodes within the 3 months following the transplantation and subclinical acute rejection episodes on the 3-month surveillance biopsies (BANFF 2011 classification); 2) the percentage of renal fibrosis on the 3-month surveillance biopsies using the computerized quantification described by Meas-Yedid et al. [19]; 3) the time between transplantation surgery and hospital discharge; 4) the evolution of the Tacrolimus trough level; 5) the hematologic monitoring within the first three months after surgery including WBC blood cell count, CD3 subpopulation analysis, and CD4, CD8, CD19, natural killer (NK) cell, and platelet counts, and 6) the occurrence of infections within the study follow-up, especially CMV and BK viruses assessed at three months by RT-PCR, as either primary or secondary infections.

### Follow-up time

Follow-up at 3 months is required for the previous endpoints for full completion of the study. Nevertheless, patients will be followed for some years after the end of the trial for incidence of cancer, post-transplant lymphoproliferative disorders, infections, graft and patient survival. This will be possible because these patients will be part of the prospective DIVAT cohort (www.divat.fr).

### Sample size

Based on the results of the randomized trial published by Noel et al. [13] and according to our previous observational study [5], we can expect 40 % DGF in patients treated with basiliximab versus 28 % in patients with ATG (odds ratio (OR) = 1.7). To respect a type I error at 0.05 and a power at 0.80 (one-tailed test), 192 patients will have to be included in each group. We therefore aim to include a total of 384 patients. We chose one-tailed testing because no paper has described a higher incidence of DGF for ATG-treated patients compared to other non-depleting induction therapies. The literature heterogeneity consists in the statistical significance of the ATG effect for preventing the DGF occurrence. Even if the two-tailed test takes into account the possibility that the reference treatment might be better [20], the one-tailed test seems the most adapted in our situation for both ethical and cost-efficiency considerations [21].

### Data acquisition

Data collection will be performed by the investigators or the clinical research assistants by using an electronic case report form accessible from the web and developed with Clinsight®. Data are anonymously extractable to keep the identities of patients confidential.

### Data analysis

Analysis will be performed by respecting the principle of intention-to-treat analysis. No intermediate analysis will be performed. Depending on the observed switches or dropouts, per-protocol analysis may be secondarily performed in order to evaluate the robustness of the findings. According to the sample size and the random assignment of treatments, both groups are expected to be comparable. In order to validate this comparability, a preliminary description of the two groups will be performed according to the mean, standard deviation and range for continuous variables, and according to percentage and effective for categorical variables. For binary endpoints, logistic regression with random intercept and/or slope will be performed to estimate the treatment effect, taking into account possible between-center differences. The same methodology will be used to assess the percentage of renal fibrosis and the time between surgery and hospital discharge. However, these will use linear models with random intercept and/or slopes. *P* <0.05 will be considered statistically significant for all tests. The statistical analyses will be performed using R software [22].

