## Methods/design

### Study design

We are conducting a phase IV, open label, randomized, multicenter prospective study, to compare ATG in parallel with a control group treated by basiliximab. The 1:1 randomized allocation of patients between groups is stratified on the clinical center, and on the hypothermic machine-perfusion device. The participation of each patient is scheduled for 3 months. The study design is outlined in Fig. 1.

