### Study population

Recruitment is performed during pre-surgery hospitalization in one of the six participating centers (Lyon, Montpellier, Nancy, Nantes, Nice, and Paris Necker). Inclusion criteria are: 1) adults with end-stage renal disease; 2) patients under hemodialysis (because the occurrence of DGF, defined by the need for dialysis within the first seven days post transplantation, is not correctly evaluated for patients on peritoneal dialysis or for patients who will receive pre-emptive transplantation); 3) patients with kidneys transplanted from deceased donors with heartbeat; 4) patients with written informed consent; 5) patients affiliated with the French social security system; 6) patients considered at low immunologic risk (i.e., first kidney transplant recipients with no anti-HLA immunization prior to transplantation and sera negative for anti HLA immunization, regardless of the technique used for this evaluation); 7) patients considered at high-risk of DGF (i.e., DGFS higher than 0.4), and 8) patients without medical contraindication to ATG (i.e., leukopenia lower than 3,000/mm^3^, thrombopenia lower than 100,000/mm^3^, previous history of cancer (except basal cell skin cancers), current history of hepatitis C virus (HCV)/hepatitis C virus (HBV)/HIV infection, or Epstein-Barr virus (EBV)-matching donor positive and recipient negative). For ethical considerations, pregnant or lactating women and patients under guardianship are not included.

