### Primary outcome measures

The primary endpoint will be the occurrence of a DGF defined as the need for dialysis within the first seven days post transplantation. This definition of DGF is the most commonly recognized and published. Nevertheless, this definition is insufficient since the decision to dialyze may not only depend on the insufficiency of the post-transplantation renal function but also on hyperhydration or hyperkaliemia for instance. The definition of the DGF will thus consider, 1) the number of days after transplantation to reach an estimated glomerular filtration rate (eGFR) above 10 mL/min, calculated using the modification of the diet in renal disease (MDRD) formula [18], 2) the evolution of the MDRD eGFR until hospital discharge, and 3) the number of dialyses performed after the transplantation without taking into account dialysis exclusively prescribed for hyperhydration or hyperkaliemia.

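### The primary DGF model is left open between a random centre intercept, a random treatment slope or both with six centres, and the 192 per group matches only a common-effect analysis

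*Protocol article*

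**What the plan says.** The primary endpoint is binary. The section on primary outcomes defines it thus: "The primary endpoint will be the occurrence of a DGF defined as the need for dialysis within the first seven days post transplantation". The Data analysis section therefore governs the primary test when it states: "For binary endpoints, logistic regression with random intercept and/or slope will be performed to estimate the treatment effect". The stated purpose is to allow for differences between centres. The same structure is carried over to the linear models for renal fibrosis and time to discharge. No rule says which random effects enter, and no covariate is named.

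Patients are recruited "in one of the six participating centers (Lyon, Montpellier, Nancy, Nantes, Nice, and Paris Necker"). On randomisation, Study design says: "The 1:1 randomized allocation of patients between groups is stratified on the clinical center, and on the hypothermic machine-perfusion device".

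The Sample size section assumes "we can expect 40 % DGF in patients treated with basiliximab versus 28 % in patients with ATG (odds ratio (OR) = 1.7") and continues: "To respect a type I error at 0.05 and a power at 0.80 (one-tailed test), 192 patients will have to be included in each group". It mentions no between-centre variation in the treatment effect.

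**The concern.** The *and/or* covers three models: intercept only, slope only, or both. I read the slope as a treatment slope, since treatment is the only explanatory variable that the sentence mentions. The three models can give different standard errors and P values for the same data. Slope-only would leave out baseline differences between centres, which is hard to square with the stated purpose.

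A random treatment slope rests on six centre-level effects. Its variance enters the standard error of the treatment effect, so a poorly determined quantity can move the primary result. The sample size makes no allowance for it. What is at stake is whether the confirmatory test is a single defined test, and whether the stated power of 0.80 belongs to the test that will be run. The stratification factor missing from the named model is a lesser part of the same problem.

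**Working it through.** **Inputs from the protocol article.** 40 % and 28 %; one-sided 0.05; power 0.80; 192 per group (Sample size). Six centres (Study population). Stratification by centre and machine perfusion (Study design).

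**Assumptions, because the document gives no values.** Between-centre SD of the treatment log odds ratio (tau) from 0 to 0.5; equal centres of 384/6 = 64 patients, 32 per arm; between-centre intercept SD of 0.3 in the simulation. The one-sided level is taken from the Sample size section, as Data analysis does not repeat the sidedness.

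**1. The plan's own figure.** Two proportions, pooled variance under the null, no continuity correction, mean proportion 0.34:

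n = [1.645·√(2·0.34·0.66) + 0.842·√(0.40·0.60 + 0.28·0.72)]² / 0.12² ≈ 191.6, rounded up to 192. Power at 192 is 0.801. The figure reproduces, and the calculation contains one common effect and no centre variance.

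**2. Adding a random treatment slope.**

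- Log odds ratio: ln[(0.40/0.60)/(0.28/0.72)] = ln 1.714 = 0.539.
- Variance without heterogeneity: [1/(0.40·0.60) + 1/(0.28·0.72)]/192 = 9.127/192 = 0.0475, so SE = 0.218.
- With a slope over six equal centres: SE = √(0.0475 + tau²/6).
- Power, z reference: Φ(0.539/SE − 1.645). For 5 df: noncentral t with noncentrality 0.539/SE and critical value 2.015.

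Example, tau = 0.3: SE = √(0.0475 + 0.0150) = 0.250; 0.539/0.250 = 2.155; Φ(2.155 − 1.645) = 0.70.

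| Assumed tau | SE | Power, z | Power, 5 df |
|---|---|---|---|
| 0 | 0.218 | 0.80 | 0.68 |
| 0.1 | 0.222 | 0.78 | 0.67 |
| 0.2 | 0.233 | 0.75 | 0.64 |
| 0.3 | 0.250 | 0.70 | 0.58 |
| 0.4 | 0.272 | 0.63 | 0.52 |
| 0.5 | 0.299 | 0.56 | 0.47 |

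**3. Check by simulation of the mixed model itself.** 400 trials per scenario (Monte Carlo SE about 0.02), one-stage logistic model fitted by quadrature, independent random intercept and slope, one-sided Wald z.

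| True tau | Power, slope model | Power, intercept only | Fitted slope SD below 0.05 | 90th percentile of fitted SD |
|---|---|---|---|---|
| 0 | 0.77 | 0.80 | 70 % | 0.41 |
| 0.2 | 0.73 | 0.785 | 60.5 % | 0.49 |
| 0.3 | 0.68 | 0.75 | 54 % | 0.57 |
| 0.5 | 0.63 | 0.75 | 33 % | 0.74 |

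The formula treats tau as known. In the simulation tau is estimated, often at zero, which is consistent with the smaller loss at tau = 0.5 (0.63 against 0.56).

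The last two columns show how little six centres say about the slope. With a true SD of 0.3, more than half the trials report almost none. With no heterogeneity at all, one trial in ten reports an SD of 0.41 or more.

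**The case against.** The strongest objection is scope. This is a journal article, the statistical analysis plan is not shown, and the exact random-effects structure is often settled there. That stands in part: nobody can say from this document that the choice is still open. But the article is not silent. It puts forward a set of alternatives for the confirmatory test, one of which its sample size does not support.

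A reader might infer three stronger things, none of which the document supports:

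- *That a slope variance cannot be estimated from six centres.* It can be fitted, and was in the simulation. The trouble is imprecision.
- *That power of 0.80 is lost whenever a slope is fitted.* With no heterogeneity and a z test it is 0.80 by formula and 0.77 by simulation. A clear shortfall needs a tau of about 0.2 or more, or a small-df reference, and the document states neither.
- *That the model will be picked after seeing the results.* Nothing in the text says so. It only fails to rule it out.

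It is also fair that part of the fall in power comes from heterogeneity itself. At tau = 0.3 the intercept-only model drops to 0.75 as well, so the like-for-like cost of the slope there is about 0.07 (0.75 against 0.68). If the effect truly varies, the wider standard error is also the honest one for inference beyond these centres. Choosing a common effect is thus a choice of inferential target, which is a reason to state it.

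**Conclusion.** The point holds in a limited form. The document leaves the primary model open between alternatives that differ in standard error and power, and does not name one of its two stratification factors in the model. Its sample size fits only the common-effect version. A fitted slope costs little if the effect is homogeneous and a z test is used (power 0.77 to 0.80). With heterogeneity, formula power is about 0.75, 0.70 and 0.56 at tau 0.2, 0.3 and 0.5, and 0.68 or lower with 5 df.

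These figures rest on assumed values of tau, equal centre sizes and, for the simulation, an assumed intercept SD. Some variation between centres is plausible, since tacrolimus timing follows local practice and the document concedes that the decision to dialyse does not depend on renal function alone. That is inference and gives no value for tau. An analysis plan not shown may already settle the choice.

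**What to change.** Before results are seen, name one primary model: logistic regression of DGF on treatment with a common treatment effect, centre as a fixed effect (six levels) and the machine-perfusion stratifier. Report treatment-by-centre variation as a sensitivity analysis. Use the same structure for the linear models.

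Fixed centre effects are affordable: the planning rates imply 192·0.40 + 192·0.28 ≈ 131 events, against five centre parameters plus treatment and perfusion. The total of 384 stands, with power of about 0.80 under a common effect. The supporting simulation used a random centre intercept and no perfusion term, so it is close to the proposed model but not identical.

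The cost is one sentence, with no change to recruitment or conduct. The downside is that the primary inference then applies to the participating centres, with heterogeneity shown separately. If the sponsor prefers a random slope, it should state the assumed between-centre SD and the reference distribution, and re-size the trial. If an existing analysis plan already fixes the model, the protocol wording need only be aligned with it.

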## Background

The current 10-year patient and graft survival of first kidney transplantation varies from 25 % to 40 % depending on inclusion criteria and countries. Therefore, much still has to be done to improve long-term outcomes for kidney transplant recipients. As part of this objective, delayed graft function (DGF) is well known among the main risk factors of poor long-term outcome, increased hospitalization duration and acute rejection [1, 2]. DGF is the major clinical manifestation of renal injuries that are linked to ischemia reperfusion injury. Until now, this has been unavoidable in kidney transplantation and occurs after cold and warm preservation of the kidney. Preventing DGF by focusing primarily on donor management, organ procurement, infusion and preservation supplies, and drug monitoring, is thus probably the most beneficial strategy for prolonged long-term graft and patient survival. Thus, the prediction of DGF is of primary importance in kidney transplantation for adapting as far as possible the medical management of high-risk transplantations.

However, although the risk factors for DGF have been well-described in the literature for a number of years, it is difficult to predict this complication in practice at an individual level. Several scoring systems have been proposed within the last few years [3, 4], but these are not used routinely for medical decision making because of the important number of included parameters or the absence of validation. Therefore, we recently proposed an alternative scoring system entitled the delayed graft function score (DGFS) [5]. The DGFS is composed of only five variables: the cold ischemia time, the donor age, the last donor serum creatinine level, the recipient body mass index, and the induction therapy used. The DGFS is associated with a good predictive capacity, with area under the receiver operator characteristic (ROC) curve at 0.73 (95 % CI from 0.68 to 0.77). By using the learning sample, we calculated a DGFS threshold value at 0.4 to obtain a positive predictive value of 40 %, an acceptable percentage to consider recipients with a high risk of DGF (the overall percentage of DGF was 25.1 %). By using the validation sample, this decision rule corresponds to sensitivity of 47.5 % (95 % CI from 40.3 to 55.0), a specificity of 83.5 % (95 % CI from 79.5 to 86.9), a positive predictive value of 57.7 % (95 % CI from 48.5 to 64.5), and a negative predictive value of 77.9 % (95 % CI from 73.7 to 81.6).

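### Allocation is stratified on centre and machine perfusion, but the stated logistic model names only centre: a small mismatch that costs little power and is nearly free to close

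*Protocol article*

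**What the plan says.** On allocation, the Study design section states: "The 1:1 randomized allocation of patients between groups is stratified on the clinical center, and on the hypothermic machine-perfusion device". The Abstract and the legend of Fig. 1 say the same. None of them gives a reason for the second factor.

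On analysis, the Data analysis section specifies for binary endpoints "logistic regression with random intercept and/or slope will be performed to estimate the treatment effect, taking into account possible between-center differences". The primary endpoint, "occurrence of a DGF defined as the need for dialysis within the first seven days post transplantation", is binary, so this is its model. The section mentions neither machine perfusion nor the DGFS.

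On the score, Study population requires a DGFS above 0.4, so every randomised patient has a value. Background lists its five components, which include "the last donor serum creatinine level, the recipient body mass index, and the induction therapy used". One component is therefore the treatment under study.

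**The concern.** An analysis normally carries the factors that restricted the randomisation. Stratifying balances the arms on a factor. If that factor is prognostic and the model omits it, the standard error takes no credit for the balance, so the test is slightly conservative and some power is lost.

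There is also a pre-specification issue. The article commits to a model family and says what the model accounts for, but names one of the two factors. Whether machine perfusion is adjusted for could then be decided after the data are seen. In a logistic model the two choices estimate different odds ratios whenever the factor is prognostic.

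The DGFS raises a lesser question. It is the trial's own predictor of the primary endpoint and is already computed, so using it as a covariate could add precision.

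**Working it through.** **1. The two statements compared.** Randomisation uses centre (six) and machine perfusion. The stated model uses centre. The mismatch is one factor.

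**2. The plan's own sample size.** The Sample size section gives 40 % versus 28 %, one-sided alpha 0.05 and power 0.80. With pooled variance under the null and no continuity correction:

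n = [z₀.₉₅ √(2·p̄·q̄) + z₀.₈₀ √(p₁q₁ + p₂q₂)]² / (p₁ − p₂)², with p̄ = 0.34

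- √(2 × 0.34 × 0.66) = √0.4488 = 0.6699
- √(0.40 × 0.60 + 0.28 × 0.72) = √0.4416 = 0.6645
- n = (1.645 × 0.6699 + 0.8416 × 0.6645)² / 0.12² = 191.6, rounded up to 192 per group

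Power at 192 is 0.801. The odds ratio is (0.40/0.60)/(0.28/0.72) = 1.71. The plan's figures reproduce. They describe an unadjusted comparison and do not depend on this point.

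**3. What the omission costs.** The documents give neither the share of kidneys on machine perfusion nor its effect on DGF, so both are assumed.

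- Design: 384 patients, six centres (assumed SD 0.3 on the logit scale), permuted blocks of 4 within centre by machine perfusion.
- Rates calibrated to 40 % versus 28 %; one-sided Wald test at 0.05; 2,500 runs per setting.
- Assumed machine-perfusion share 30 % or 50 %, and odds ratio for DGF 1.0, 0.6, 0.4 or 0.25.
- Assumed residual spread of the baseline score on the logit scale: SD 0.3 or 0.6.
- Centre was fitted as a fixed effect in place of the plan's random intercept.

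Each range covers four settings (two shares by two score SDs).

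| Machine-perfusion OR | Power, centre only | Gain from adding machine perfusion (points) | Gain from adding machine perfusion and score (points) |
|---|---|---|---|
| 1.0 | 0.793–0.811 | 0.08–0.12 | 0.56–3.16 |
| 0.6 | 0.794–0.810 | 0.16–0.56 | 0.88–2.68 |
| 0.4 | 0.796–0.804 | 0.68–0.96 | 1.24–3.64 |
| 0.25 | 0.802–0.825 | 1.48–2.24 | 2.08–4.52 |

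The gain from both covariates depends mostly on the assumed score spread: 0.6 to 2.2 points at SD 0.3, and 2.1 to 4.5 at SD 0.6.

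**4. Type I error.** The centre-only model gave 0.044 to 0.055. With machine perfusion added it was 0.044 to 0.061, and with both covariates 0.046 to 0.058. The Monte Carlo standard error is √(0.05 × 0.95/2500) = 0.004. At odds ratio 0.25 the adjusted test also rejected somewhat more often under the null (for example 0.061 against 0.050), so part of the roughly 2-point gain there may reflect that.

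**5. Monte Carlo precision.** Each power has a standard error of √(0.8 × 0.2/2500) = 0.8 point. The models were fitted to the same simulated trials, so their differences are less noisy than that, but the second decimal should not be relied on. A separate run (3,000 replicates, 50 % on machine perfusion, odds ratio 0.5 or 0.6, score SD 0.3 to 0.7) agrees: 0.817→0.820→0.829, 0.800→0.807→0.821 and 0.793→0.800→0.828. That is 0.3 to 0.7 point for machine perfusion and a further 0.9 to 2.8 for the score.

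**The case against.** The strongest reply is that this is one sentence in a condensed article. The mention of centre explains the random terms; it does not say that no other fixed effects will be used. Covariate lists are commonly set in a statistical analysis plan, which is not shown and may already include machine perfusion. This stands as a limit: the article does not exclude the factor. It does not remove the point, because the article states what the model takes into account and that statement covers one of the two factors.

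Several stronger readings are tempting, and the documents do not support them:

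- **That the primary test is invalid.** Omitting a balanced factor does not inflate type I error, and the simulation shows no inflation.
- **That the trial becomes underpowered because 191.6 was rounded to 192.** The sample size was computed for an unadjusted comparison, and centre-only power in the simulation stays around 0.80. Only an extra gain is forgone.
- **That the sponsor regards machine perfusion as prognostic for DGF.** The article gives no reason for choosing it. At odds ratio 1.0, adding it gains almost nothing.
- **That omitting the DGFS is a design mismatch.** It was not a stratification factor, so adjusting for it is optional. Its range is cut at 0.4 by eligibility, which limits the gain, and nothing in the article says it predicts rejection, fibrosis or infection.

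It is also fair to object that adjustment changes the quantity estimated. The plan's odds ratio of 1.7 comes from marginal rates, whereas an odds ratio adjusted for prognostic covariates is conditional. This stands and is handled in the fix.

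**Conclusion.** The point holds as a minor inconsistency between design and stated analysis. Its value lies mainly in pre-specification. The power at stake from machine perfusion is about 0.1 point if the factor is not prognostic, 0.2 to 1 point at odds ratios of 0.6 to 0.4, and about 2 points at 0.25. With the DGFS as well, the total is about 0.6 to 4.5 points. All of this rests on an assumed machine-perfusion share, odds ratio and score spread, and on centre fitted as a fixed rather than random effect. The test as stated is at most slightly conservative, and the 192 per group needs no change.

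**What to change.** Add one sentence to the Data analysis section naming machine perfusion (yes/no, as randomised) as a fixed effect beside the centre effect in the primary DGF model. If an analysis plan already does this, align the two texts.

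Optionally, and for the primary endpoint only, pre-specify the baseline DGFS as a further covariate. Because the score contains the induction therapy, compute it with the same induction setting for every patient, or enter its four non-treatment components instead. Otherwise the covariate would carry part of the treatment effect.

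Report the marginal risk difference beside the adjusted odds ratio, so that the result can be set against the planned 40 % versus 28 % (12 percentage points).

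The cost is a few lines of text. The perfusion stratum is recorded in order to randomise and the score in order to screen, so no new data or patients are needed. The change should be made before outcome data are examined by arm.
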